#### Maternal primary outcome measures

The *Edinburgh Postnatal Depression Scale (EPDS)* [74] is a 10 item self-report questionnaire designed to assess the cognitive and affective symptoms of depression and anxiety over the previous 7 days. The EPDS is the most widely used screening questionnaire for postpartum depression [75] in both research and clinical practice and has also been validated as a screening measure for probable depression during pregnancy [76–78]. Each item on the EPDS is rated on a four-point scale, with a total score ranging from 0 to 30, with higher scores indicating greater levels of distress. A cut off score of 13 has been found to have the optimum specificity and sensitivity in detecting an incidence of major depression in the postnatal period [74]; however, cut off scores during the antenatal period are controversial and culturally dependent; ranging from 4.5 to 13.5 [79]. Despite disagreements in the cut off score for the incidence of major depression during the antenatal period, a cut off score of ≥13 will be used in this study to identify the incidence of perinatal depression. A cut-off score of ≥13 has been used in prevalence studies in New Zealand [5, 6] and has been shown to not miss any women in need of help for their mood in Australian clinical practice [80]. A cut off score of 10 has been shown to be optimal to identify the presence of minor depression in postnatal populations [74]. For this purpose and given the variability of cut-off scores to identify antenatal depression in particular, the present study will use a score of 10–12 to identify minor depression and anxiety and ≤ 9 to identify the absence of perinatal depression and anxiety.

The *Clinical Global Impressions – Improvement Scale (CGI-I)* [81] is a clinician-rated assessment of the change in participant’s symptoms from baseline ranging from 1 (very much improved) to 7 (very much worse). The CGI-I will be administered by graduate students under the supervision of a clinical psychologist and will assess mood, anxiety and global improvements. Participants enrolled in the clinical trial will be asked to rate their own improvement in mood, anxiety and globally at the end of the 12-week RCT phase and again every 4 weeks during the OL phase. The CGI-I has demonstrated high external validity (r = 0.74) [82] and is widely used in clinical trials.

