### Data analysis

Demographic characteristics will be compared across the treatment groups using independent samples *t*-tests in order to test for potential failures of randomization.

For the primary outcomes (EPDS and CGI-I scores), the repeated measures of the outcome variables will be modelled using generalized linear mixed effects regression models using Stata 15 [140]. These models will permit the testing of differences between the multinutrient group and the active control group over the course of the trial. In the case of the EPDS, baseline scores will be used as a covariate factor. For secondary outcomes (e.g. MADRS, DASS), linear mixed effects models will also be used.

The pooled mean scores (and standard deviations) over the course of the trial on each of the primary outcomes will be used to compute estimates of effect size (Cohen’s *d*). Clinical significance between groups will be identified by a minimum of a three point difference in EPDS scores. Clinical significance within groups will be identified by a four point change on the EPDS as described by Matthey [141]. A clinical significant change will be categorised as the following: ‘Recovered’: participants who move from a score of 13 or more at baseline to 11 or less following treatment and whose score has reduced by four points; ‘Improved’: participants whose baseline score reduces by four points post treatment but is still above 13 or more; ‘Deteriorated’: participants whose baseline score increases by four points post treatment; ‘No change’: participants whose pre-post score is less than a four point change.

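### The four EPDS clinical-change categories are not exhaustive: a woman who falls by 4 or more points and ends at 12 belongs to none of them

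*Protocol article*

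**What the plan says.** In the protocol article, Data analysis, within-group clinical significance is a four-point change on the EPDS. Each woman is then given one of four labels:

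- The 'Recovered' label covers "participants who move from a score of 13 or more at baseline to 11 or less following treatment", provided that the drop also amounts to four points.
- The 'Improved' label is for "participants whose baseline score reduces by four points post treatment but is still above 13 or more".
- The 'Deteriorated' label is for a rise of four points.
- The 'No change' label goes to "participants whose pre-post score is less than a four point change".

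The section on maternal primary outcome measures describes the EPDS as a ten-item scale "with a total score ranging from 0 to 30" and sets severity bands. A score of 13 or more marks depression, and the study uses "a score of 10–12 to identify minor depression and anxiety and ≤ 9 to identify the absence of perinatal depression and anxiety". The eligibility criteria require 13 or more at entry. The registration table (Table 2) lists the EPDS at screening and again at baseline.

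**The concern.** The upper limit for 'Recovered' is 11 and the lower limit for 'Improved' is 13. EPDS totals are whole numbers, so 12 lies between the two. A woman who ends there after a fall of four or more cannot be 'No change' either, because her change is not less than four. The only categories that require a fall of four or more therefore both miss her.

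There is a second, smaller gap. 'Recovered' requires a baseline of 13 or more. A woman who qualified at screening but scored below 13 at baseline, and who then falls by four or more, ends at 8 or lower. She is neither 'Recovered' (baseline too low) nor 'Improved' (final score below 13).

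At stake is the clinical-change table for one of the two primary outcome measures. As written it cannot be completed for every participant, although the same section says the analysis will include all participants. The women left out are not a neutral group: they all improved by the amount the trial calls clinically significant.

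**Working it through.** **Inputs from the protocol article.** Baseline b and post-treatment score p are whole numbers from 0 to 30. The entry threshold is 13. 'Four points' is read as at least four, since 'No change' is defined as less than four. The garbled lower limit for 'Improved' is read as 13 or more, in line with the entry threshold and the depression cut-off; this reading leaves the smaller gap.

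**Rules applied.**
- Recovered: b ≥ 13, b − p ≥ 4, p ≤ 11
- Improved: b − p ≥ 4, p ≥ 13
- Deteriorated: p − b ≥ 4
- No change: |b − p| < 4

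**One case.** b = 16, p = 12: the fall is 16 − 12 = 4, so not 'No change'; 12 > 11, so not 'Recovered'; 12 < 13, so not 'Improved'; the score did not rise, so not 'Deteriorated'.

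**All cases with b ≥ 13.** There are 18 baselines (13 to 30) × 31 final scores (0 to 30) = 558 pairs. No pair falls in two categories. Pairs with no category: p = 12 with b from 16 to 30, which is 30 − 16 + 1 = 15. If the 'Improved' limit were read as strictly above 13, pairs with p = 13 and b from 17 to 30 would be added: 15 + 14 = 29.

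**Cases with b < 13.** A fall of at least 4 is possible for b = 4 to 12, with b − 3 possible final scores each: 1 + 2 + … + 9 = 45 pairs, all without a category.

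**From pairs to women.** The article gives no EPDS mean or SD, so the following is an assumption: baseline mean 16 to 17, SD 3; mean fall 4 to 6, SD 4.5; the fall independent of baseline; scores rounded and kept within 0 to 30.
- Ending at 12 after a fall of at least 4: 4.3% to 5.5% of women, so 0.043 × 120 = 5.2 to 0.055 × 120 = 6.6. Excluding baselines below 13 keeps the result at about 5 to 7 of 120.
- Baseline below 13 with a fall of at least 4: about 4 to 10 of 120 without that exclusion. The assumed normal curve itself puts about 8 to 15 of 120 women below 13. If every baseline is 13 or more, the count is 0. The supportable range is 0 to about 10.

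**The two sets of cut-offs side by side.**

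| Final score | Severity band | Change label after a fall ≥ 4 from b ≥ 13 |
|---|---|---|
| ≤ 9 | absence | Recovered |
| 10–11 | minor depression and anxiety | Recovered |
| 12 | minor depression and anxiety | none |
| ≥ 13 | depression | Improved |

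Of the 213 'Recovered' pairs, 33 end at 10 or 11. Under the same assumed distributions, about 25% to 33% of women labelled 'Recovered' would end there.

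**The case against.** The strongest reply concerns scope. The categories describe within-group change. The primary EPDS analysis is a mixed model on the score with baseline as covariate, and clinical significance between groups has its own three-point rule. No test or decision is tied to the four labels. This stands, and it limits the weight of the point.

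It can also be said that the full protocol or an analysis plan may state how a final score of 12 is handled, and that the data analyst is blinded, so even a late choice would hardly favour one arm. Both are fair. A reader should not infer that the gap will be filled with an eye on the results. But the article does not leave the rule to another document: it states one, and the stated rule fails on its own terms.

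A tempting stronger reading is that the recovery rate is overstated, because scores of 10 and 11 count as 'Recovered' while the article elsewhere says "the present study will use a score of 10–12 to identify minor depression and anxiety". The document does not support that. The bands describe a state at one time, whereas 'Recovered' describes a change in a woman who started at 13 or more, and the two may use different thresholds. The article itself calls antenatal cut-offs controversial, and the source cited for the four-point change is not at hand to show where 11 comes from. What remains is that two passages use different limits without explanation, and a reader of the results will need both figures.

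The loose wording of the four-point fall and of the 'Improved' limit is not a separate defect. The 'No change' rule settles the first, and the cut-off of 13 used for entry and for depression settles the second.

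**Conclusion.** The point holds as a defect in a stated rule. For women with a baseline of 13 or more, the four categories miss every fall of at least four that ends at exactly 12. That follows from the text alone and needs no assumption about the data. The likely size, about 5 to 7 of 120 women, rests on the assumed means and SDs; those women are all responders by the trial's four-point criterion. The gap for baselines below 13 is also real in logic, because the EPDS is taken at both screening and baseline. Its size is uncertain, from 0 to about 10 women.

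It should be corrected, but it is a matter for the descriptive clinical-change table only. A reader might infer that the primary comparison or the planned 120 is in doubt; neither uses these categories. Nor do the documents show that 11 is the wrong limit for 'Recovered', only that its relation to the severity bands is unexplained.

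**What to change.** Restate the categories so that each woman has exactly one:

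- Recovered: baseline 13 or more, fall of at least 4, final score 11 or less (the stated limits).
- Improved: fall of at least 4 that does not meet 'Recovered'. For a baseline of 13 or more this means a final score of 12 or more.
- Deteriorated: rise of at least 4.
- No change: change of 3 or less in either direction.

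Show women with a baseline below 13 on a separate line. To reconcile the change labels with the severity bands, report next to 'Recovered' the proportion with a fall of at least 4 and a final score of 9 or less. This leaves the trial's definition of recovery as it is and lets readers see both thresholds.

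The cost is a few words in the Data analysis section and one or two extra lines in a table. No new data are needed, and the primary model and sample size stay as they are. The change should be made before the blind is broken.

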## Methods/design

### Trial design

This randomized, double-blind, controlled trial is designed to compare the efficacy and safety of a broad-spectrum multinutrient formula to an active control formula for the treatment of depressive and anxiety symptoms in pregnant women, allocated in a 1:1 ratio. The 12 week RCT phase of the trial will be followed by an open label phase where participants can take the multinutrient intervention until the birth of their infant. The open label phase was included in order to provide participants with the opportunity to try the nutrients regardless of the random allocation in the RCT phase without breaking the blind. Participants will be followed up naturalistically until 12 months postpartum.

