### Sample size

This study aims to recruit 120 participants. In 2014, Christchurch New Zealand had 6575 live births [136]. Assuming at least 12% of pregnant women meet criteria for depression / anxiety and accounting for 1 in every 100 pregnancies being twin births, approximately 781 women per year would be eligible for the proposed study in Christchurch alone. A placebo-controlled RCT providing multinutrient supplementation to adults with ADHD [73] showed a between groups effect size of 0.64 on a measure of depression. Other RCTs found a between groups effect size of 0.39 on the EPDS when comparing a multinutrient supplement with a placebo in healthy postnatal women [137] and an effect size of 0.88 on depression outcomes from use of a B vitamin complex compared with placebo for participants with major depressive disorder [138]. Based on these findings, to detect a medium to large effect (0.6) using a two-tailed significance level of 0.05 and a power of 0.8, 45 participants per group would be needed. Assuming an attrition rate of 30% based on the mean dropout rate from the pregnant and postnatal population, 60 participants per group would provide optimal power.

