All data will be analysed on an intention-to-treat basis using the last observation carried forward method and as such will include all participants’ data regardless of treatment compliance. Treatment adherence will be measured by the total number of capsules consumed throughout the trial phases. Only participants who consume 70% or more of the total number of capsules will be considered adherent to the treatment. A per-protocol analysis, which excludes participants with protocol violations (e.g. drop out, non-adherence to treatment consumption) will be performed on the primary outcomes (EPDS and CGI-I) in order to compare differences in treatments responses between participants who were adherent with the treatment and those who discontinued participation or were non-adherent. Outcomes from the open label phase will be compared to the group outcomes from the week 12 observation of the RCT phase using generalised linear mixed effects regression models taking into account participants self-reported use of micronutrients.

To assess the effect of the multinutrient intervention has on infant development, we will compare those infants exposed to the multinutrients versus those infants not exposed to the multinutrients on emotional, cognitive and physical development. Length of exposure to the multinutrients (due to the RCT phase and varying starting points during gestation) and score on the EPDS will also be considered as continuous variables in considering infant outcomes. Hierarchical regression analysis will be run using Stata 15 in order to identify if perinatal/postpartum depression and multinutrient exposure are predictors of improved self-regulation of the infant across the various time points. Descriptive statistics for each participant will be used to compare demographic characteristics between the treatment groups to allow any differences to be controlled.

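### Carrying the last observation forward into the mixed-model analysis can bias the EPDS contrast in either direction, and dilutes a true effect, if mean scores change over the 12 weeks

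*Protocol article*

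**What the plan says.** All references are to the protocol article.

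- **Model (Data analysis).** For EPDS and CGI-I, "the repeated measures of the outcome variables will be modelled using generalized linear mixed effects regression models using Stata 15". For EPDS, "In the case of the EPDS, baseline scores will be used as a covariate factor".
- **Missing data (Data analysis).** "All data will be analysed on an intention-to-treat basis using the last observation carried forward method". This covers the primary outcomes. No other missing-data method is named and no sensitivity analysis for LOCF is planned. The only alternative analysis is per-protocol, which removes dropouts.
- **Expected loss (Sample size).** "Assuming an attrition rate of 30% based on the mean dropout rate from the pregnant and postnatal population". No split by arm and no timing is given.
- **Visits (Table 2).** EPDS is taken every two weeks until birth and CGI-I every four weeks.
- **Threshold (Data analysis).** "Clinical significance between groups will be identified by a minimum of a three point difference in EPDS scores".
- **Exits linked to outcome.** The Intervention section withdraws women who start psychiatric medication. Safety monitoring and reporting allows early open-label treatment or withdrawal when symptoms worsen.

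**The concern.** Intention to treat settles who is analysed and in which arm. It does not require filling in missing scores. A mixed model fitted by likelihood keeps every randomised woman with at least one usable visit and is valid under missing at random. LOCF replaces that assumption with a stronger one, that symptoms stay fixed at the last visit, and then treats the copied values as data.

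That assumption is doubtful here. Women enter with EPDS of 13 or more, so scores should fall through regression to the mean alone, and the Aims section expects further improvement on active treatment. At 30% attrition about 0.30 × 120 = 36 women would carry copied scores. A woman last seen at baseline would contribute up to six copied EPDS values. The primary contrast, Cohen's *d* and the Recovered/Improved/Deteriorated/No change categories would all inherit them.

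**Working it through.** **1. The plan's own figure.** The article plans "to detect a medium to large effect (0.6) using a two-tailed significance level of 0.05 and a power of 0.8, 45 participants per group". The normal approximation gives 2 × (1.96 + 0.84)² / 0.6² = 43.6, so 44. The two-sample *t*-test gives 44.6, so 45. The figure reproduces.

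**2. Inputs.**
- From the article: 60 per arm, 1:1 allocation, EPDS at weeks 0, 2, …, 12, 30% attrition overall, and a 3-point threshold.
- Assumed, because the article does not give them: SD, mean trajectory, dropout split by arm and dropout timing.

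**3. Expected LOCF contrast at week 12.** Let the mean change be linear, reaching *c* at week 12. A proportion *d* drops out, unrelated to outcome, with the last visit equally likely at weeks 0, 2, …, 10. A dropout then shows on average (0 + 2 + 4 + 6 + 8 + 10)/6 ÷ 12 = 5/12 of the change, so

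LOCF mean change = *c* × [(1 − *d*) + 5*d*/12] = *c* × (1 − 7*d*/12).

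- No effect, both arms −6, dropout 40% active / 20% control: −6 × 0.767 = −4.6 against −6 × 0.883 = −5.3. False difference 0.7 points against active. Swapping the dropout rates reverses the sign.
- No effect, 25% / 35%: 6 × (7/12) × 0.10 = 0.35.
- No effect, 30% in each arm, but active dropouts last seen at week 0 or 2 (share 1/12) and control dropouts at week 8 or 10 (share 9/12): −6 × 0.725 = −4.35 against −6 × 0.925 = −5.55. False difference 1.2.
- True difference −3, equal 30%: −3 × (1 − 0.175) = −2.475, whatever the two trajectories are.
- True difference −3 (−8 against −5), 40% active / 20% control: −6.13 − (−4.42) = −1.72.
- The same with 20% active / 40% control: −7.07 − (−3.83) = −3.23, an overstatement.
- Flat means (*c* = 0): every LOCF mean change is 0, so there is no bias.

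**4. Averaged over the six post-baseline visits.** Express the change in sixths, one per fortnight. A completer's visits sum to 1 + 2 + … + 6 = 21. A woman last seen 0, 1, …, 5 fortnights in has LOCF sums of 0, 6, 11, 15, 18 and 20, mean 11.67. Loss per dropout = (21 − 11.67)/36 = 0.259 of *c*. With *c* = −6 and 20% / 40%, the false difference is 0.259 × 6 × 0.20 = 0.31.

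**5. Simulation, EPDS only.** Random-intercept SD 3, week-12 slope SD 4 and residual SD 2.5, so the week-12 SD is √(9 + 16 + 6.25) = 5.6. Dropout was unrelated to outcome, with 1,500 to 3,000 replicates. LOCF at week 12 was analysed by baseline-adjusted ANCOVA. The comparator is a likelihood repeated-measures model with known covariance, fitted to observed visits only.

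| Scenario | LOCF | Observed-data model |
|---|---|---|
| No effect, both −6, 20% / 40%, week 12 | 0.7 points, 11–12% rejection | about 0, about 5% |
| Same, averaged over visits | about 0.3, 7–8% | not run |
| No effect, 25% / 35%, week 12 | about 0.3, about 7% | not run |
| No effect, both −3, 20% / 40%, week 12 | 0.38, 7.7% | not run |
| True 3, equal 30% | 2.4–2.5, power 71–76% | about 3.0, power 81–83% |
| True 3, 40% active / 20% control | about 1.7, power about 43% (another run: 1.6 and 39%) | about 3.0, power 81% |
| True 3, 20% active / 40% control | 3.3 | about 3.0 |

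**6. Sensitivity to the assumptions.** A second set of 600 replicates used SD 5 (3 / 0.6), a baseline-to-week-12 correlation of 0.5 + 0.5 × 0.7⁶ = 0.56, and constant dropout risk per interval.
- No effect, both −6, 20% / 40%: false difference about 0.8 with 17–19% rejection, against 5–6% for the observed-data model.
- Dropout also dependent on the last score (about 45% against 20%): 1.3 points and 36%, against at most 0.05 points and 4.8%.
- Flat means with random dropout: bias within simulation error.

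**The case against.** Several counter-arguments are sound and limit the claim.

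- **Bias is conditional.** A reader might infer that LOCF is biased whenever dropout differs by arm, or that the arm losing more women always looks worse. Neither follows. With flat means and random dropout there is no bias, and the arm with more dropout looks worse only if scores are improving. Improvement is likely here, but the article gives no trajectory.
- **The calculation is one reading of the analysis.** The article models repeated scores and pools them for Cohen's *d*. It does not say whether the contrast is at week 12 or averaged. The averaged contrast roughly halves the bias but does not remove it.
- **The dropout splits are stress cases.** The article gives 30% overall and nothing by arm, so it does not show that dropout will differ.
- **Power.** A reader might compare about 89% with no dropout against about 74% under LOCF and charge the whole loss to LOCF. Part of that loss comes from dropout itself. Against an observed-data analysis of the same incomplete data, LOCF costs roughly 7 to 11 percentage points.
- **CGI-I was not simulated.** The reasoning carries over, and a woman leaving before week 4 has no post-baseline rating to carry forward. No size can be quoted.
- **The alternative also has an assumption.** Missing at random is uncertain when some exits follow worsening or psychiatric medication. That supports adding a sensitivity analysis. It does not rescue LOCF, which freezes those women at their exit score.

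LOCF cannot be defended as conservative: under the assumptions above it moves a true 3 points down to 1.7 or up to 3.3, depending on which arm loses more women. Nor is this a detail left to an analysis plan, because the article states the rule and applies it to all data.

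**Conclusion.** The point holds in conditional form. The article imposes LOCF on an analysis that does not need it. If mean EPDS changes over the 12 weeks, the contrast is biased in either direction when dropout rate or timing differs by arm, and a true effect is diluted when dropout is equal.

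The dilution under equal dropout needs no difference between arms: at the article's own 30%, with uniform dropout times and linear change, a true effect at its 3-point threshold is estimated below that threshold. The type I error figures do need unequal dropout. They run from about 7% for mild imbalance or an averaged contrast, through 11–12% for 20% against 40% at week 12, to 17–19% under the second covariance model. All sizes depend on assumed SD, trajectory and dropout pattern. They illustrate what the rule can do and do not predict this trial's result.

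**What to change.** - Delete the LOCF clause from the intention-to-treat sentence. State instead that all randomised women are analysed in their allocated arm, with the mixed model fitted by maximum or restricted maximum likelihood to all observed visits and no single imputation.
- Add a missing-not-at-random sensitivity analysis of week-12 EPDS, for example delta-adjusted or reference-based multiple imputation, because some exits are tied to worsening or psychiatric medication.
- Classify dropouts in the Recovered/Improved/Deteriorated/No change categories from the same multiple imputations. Otherwise, deleting LOCF leaves them with no rule.
- Keep LOCF, if at all, as a labelled sensitivity analysis.

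The cost is a change of wording and a little extra analysis work. The planned Stata models run on incomplete series without imputation, and no data collection changes. The change should be fixed before unblinding.

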### Intervention

Participants will be randomly assigned to receive either a multinutrient formula (Daily Essential Nutrients (DEN)) or an active control formula containing iodine and riboflavin for a 12-week period in order to allow enough time for the treatment to reach a substantial effect. Iodine is recommended to be taken throughout the duration of pregnancy in New Zealand and will therefore be used as an active control so that an additional iodine supplement will not need to be taken alongside the study interventions.

The full dose of 12 capsules will be taken as four capsules three times daily. Titration to the full dose will occur over a 7-day period whereby participants take one capsule, three times each day with the dose increasing by three capsules every second day until the maximum dose is achieved. Taken at the full dose, both formulas provide the daily supplemental intake of iodine for pregnant and lactating women as recommended by the New Zealand Ministry of Health. The dose of iodine in the active control formula will be distributed across 12 capsules such that participants randomized to the active control condition consume the same number of capsules. The multinutrient formula contains riboflavin (vitamin B_2_), a vitamin known to colour the urine. Riboflavin will be added to the active control formula to mimic the possible effect on urine colour in order to maintain the double-blind.

Both the multinutrient and the active control formulas are similar in appearance and will be taken orally in capsule form. They will be packaged in white opaque bottles containing two vanilla sachets to ensure all the capsules smell the same. Each bottle will have a label identifying the participant number. Both formulas are suitable for participants with intolerances or allergies to gluten, dairy and soy. The full list of ingredients and doses can be viewed in Table 1.

**Table 1 Tab1:** Intervention ingredients

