**Active Control Supplement Facts**	
Amount per serving (12 capsules)	
Riboflavin	1.2 mg
Potassium Iodide	150 mcg
Silicon dioxide	30 mg
Magnesium stearate	60 mg
Microcrystalline cellulose	6 g

DEN was chosen for this study as the combination of nutrients it contains is the most studied combination in the world for the treatment of psychiatric illnesses [51] and has found robust effects on a range of psychological symptoms that are also implicated in antenatal depression and anxiety [52, 69–72]. Furthermore, the safety and tolerability of this combination of multinutrients is well documented in both adults and children [72, 73].

During the RCT phase of the trial, participants will be able to continue taking omega 3 and probiotic supplements if they were taking these prior to screening for the trial. Participants will also be able take iron, if needed, at any time during the pregnancy and will be able to continue any form of psychotherapy that had begun prior to screening. Participants will be withdrawn from the study if they are prescribed and take any psychiatric medication given the potential interaction with nutrients. Participants will be encouraged before enrolment in the trial to avoid taking additional nutrients, other than those needed for medical reasons, throughout the duration of the trial in order to minimize the risk of adverse events. However, they may be withdrawn from the trial if the dose of a prescribed vitamin or mineral supplement exceeds the upper limit. Decisions on continued participation in the trial will be made on a case-by-case basis. The upper limit is the maximum dose of a nutrient that can be taken without any adverse effects.

Following the 12-week RCT period, all participants will be invited to enter an open label phase until the birth of their infants and where the capsule dose will be identical and follow the same titration procedure as the RCT phase. The product is commercially available for participants to purchase should they wish to continue taking the multinutrients post-trial.

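### The 70% adherence rule for the per-protocol analysis counts capsules over all trial phases, so open-label intake after week 12 can decide who is adherent in the randomised comparison

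*Protocol article*

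**What the plan says.** The Data analysis section of the protocol article sets the rule in two sentences: "Treatment adherence will be measured by the total number of capsules consumed throughout the trial phases", and then "Only participants who consume 70% or more of the total number of capsules will be considered adherent to the treatment". The next sentence puts it to use: "A per-protocol analysis, which excludes participants with protocol violations (e.g. drop out, non-adherence to treatment consumption) will be performed on the primary outcomes", namely EPDS and CGI-I.

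Capsules are taken in two phases. The Trial design section states that "The 12 week RCT phase of the trial will be followed by an open label phase". It then says what the second phase offers, whichever arm a woman was randomised to: "participants can take the multinutrient intervention until the birth of their infant". The Intervention section (text after Table 1) makes open label an offer: "all participants will be invited to enter an open label phase until the birth of their infants". It adds that "the capsule dose will be identical and follow the same titration procedure as the RCT phase".

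Nothing in the article limits the adherence count to the 12 randomised weeks or applies the 70% to each phase in turn. The paragraph that holds the rule names the RCT phase and the open-label phase individually when it means one of them. The adherence sentence instead uses the plural, one total and one threshold.

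**The concern.** The randomised contrast ends at week 12. A per-protocol analysis of that contrast should select women on what they did with the randomised product while the contrast was running. A pooled count brings in behaviour that comes later and differs in kind:

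- Open-label intake follows the week-12 assessment, is voluntary, and may depend on how the woman felt by then. Selecting on it conditions the set on something that happens after the outcome.
- For women randomised to control, open-label capsules are a different product. Multinutrient capsules would count towards adherence to iodine and riboflavin.
- Entry is allowed from 12 to 24 weeks of gestation, so the open-label phase is long for some women and short for others. The same 70% is then a different test of randomised-phase adherence from one woman to the next.

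At stake is whether the one planned per-protocol analysis of both primary outcomes can be interpreted.

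**Working it through.** The plan gives no capsule totals, and its 70% is a definition, so there is no figure of its own to reproduce. The check counts capsules due from the stated schedule and asks what the pooled rule does.

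**Inputs from the protocol article**
- Full dose, Intervention section: "The full dose of 12 capsules will be taken as four capsules three times daily".
- Titration, same section: start at three capsules a day and add three every second day, over 7 days.
- Open label: same dose and same titration.
- Entry: 12 to 24 weeks of gestation (Eligibility criteria). The randomised phase lasts 12 weeks and open label runs to birth.

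**Assumption not in the document:** birth at 40 weeks, with 37 weeks as a check. Open label is taken to start as soon as the 12 weeks end.

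**Step 1. Randomised phase.** First week: 3+3+6+6+9+9+12 = 48. The other 77 of 84 days at 12 a day: 924. Total due: 48 + 924 = **972**.

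**Step 2. Open label, birth at 40 weeks.** Days = (40 − 12 − entry week) × 7. Capsules due = 48 + 12 × (days − 7).
- Entry at 12 weeks: 112 days, 48 + 12 × 105 = **1308**
- Entry at 18 weeks: 70 days, 48 + 12 × 63 = **804**
- Entry at 24 weeks: 28 days, 48 + 12 × 21 = **300**

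**Step 3. Pooled score.** Score = (randomised taken + open-label taken) / (972 + OL), where OL is the number of open-label capsules due.

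| Entry (weeks) | Pooled capsules due | Score: all randomised, no open-label capsules taken | Least randomised adherence that passes with full open-label intake |
|---|---|---|---|
| 12 | 2280 | 972/2280 = 43% | (0.7×2280 − 1308)/972 = 30% |
| 18 | 1776 | 972/1776 = 55% | (0.7×1776 − 804)/972 = 45% |
| 24 | 1272 | 972/1272 = 76% | (0.7×1272 − 300)/972 = 61% |

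The third column is for a woman who enters open label and then takes none of its capsules.

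**Step 4. Birth at 37 weeks.** Entry at 12 weeks gives 13 open-label weeks and 48 + 12 × 84 = 1056 capsules. Entry at 24 weeks gives one week and 48 capsules.
- Least passing randomised adherence with full open-label intake: (0.7×2028 − 1056)/972 = 37% and (0.7×1020 − 48)/972 = 69%.
- Score with all randomised and no open-label capsules: 972/2028 = 48% and 972/1020 = 95%.

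The effect shrinks with earlier birth and nearly vanishes for the latest entrants, but it stays large for early entrants.

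**Step 5. Less extreme cases.** Entry at 16 weeks, birth at 40: 972 capsules are due in each phase, 1944 in all.
- Half the randomised capsules and 95% of the open-label ones: (486 + 923.4)/1944 = 72.5%, adherent.
- 90% of the randomised capsules and 40% of the open-label ones: (874.8 + 388.8)/1944 = 65%, non-adherent.

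The woman who took more of the randomised product is the one excluded. With birth at 37 weeks the same two women score 69.1% and 68.7%, so both fall just short.

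**Step 6. Count to week 12 only.** The denominator is 972 for every woman, and 70% is 680.4, so at least 681 capsules. Open-label intake no longer matters.

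**The case against.** The strongest reply is that the pooled reading is an inference. The sentence may only mean that capsules are counted in both phases, with the 70% applied within each. Returns are collected every 4 weeks in both phases, and the article condenses a longer protocol that may define the denominator. That reading is possible, but it is not the natural one, because the text gives one total and one cut. An analyst working from the words would build the pooled set, so the sentence needs changing on either reading.

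A second reply is that the article does not tie the per-protocol analysis to week 12, and Table 2 lists EPDS and CGI-I up to birth and postpartum. However, the same section gives open-label outcomes their own analysis against the week-12 observation. A single membership rule cannot serve both a randomised comparison and a later period in which all entrants take the multinutrient.

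Several stronger readings are tempting and do not stand:
- A reader might infer that a fully adherent woman who declines open label is excluded. The article does not say that capsules from a phase she never entered were due to her. If they were not, she scores 100%.
- A reader might infer that the set will generally keep women who took less than half their randomised capsules. With birth at 40 weeks and complete open-label intake, entry at 20 weeks (636 open-label capsules) already needs (0.7×1608 − 636)/972 = 50.4%. The case therefore requires entry before about 20 weeks and near-complete open-label intake.
- A reader might infer a known direction of bias in the treatment effect. Nothing in the document allows one to be given.

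**Conclusion.** The point holds in a limited form. As worded, the adherence rule pools the randomised and open-label phases, and open-label intake can change a woman's per-protocol status in either direction. The effect is largest for early entrants. With birth at 40 weeks and entry at 12 weeks, full randomised adherence can score as low as 43%, and randomised adherence of 30% can pass. With entry at 24 weeks the corresponding figures are 76%, which passes, and 61%. With birth at 37 weeks the least passing randomised adherence runs from 37% to 69% across the entry range.

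These results rest on the plain reading of the two sentences, the stated capsule schedule, and an assumed date of birth. They describe what the rule permits; the document gives no means of saying how many women would be affected. For women who never enter open label the denominator is undefined, and no figure is claimed. The intention-to-treat analysis, which includes women regardless of compliance, is not touched. The rule should be corrected before the per-protocol set is built, but it does not threaten the main result.

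**What to change.** For the per-protocol analysis of the randomised phase, define adherence as capsules taken (dispensed minus returned) from first dose to the week-12 visit, divided by the capsules scheduled for that period. Apply the existing 70% cut to that figure. Report open-label adherence separately, with its own denominator and only for women who enter that phase.

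The cost is a sentence or two in the analysis plan. Unused capsules are already returned at the 4-weekly visits (Trial phase and follow up section), so the week-12 count needs no new data.
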